### Randomisation and blinding

Within each municipality, schools will be randomised 1:1 to group 1 (Basic: bundle 1) or group 2 (Enhanced: bundle 1 + 2) using a computer-generated assignment by an independent statistician after baseline measurement has been conducted in September 2021. It is not possible to blind school staff and the research team to allocation, but parents and children will not get this information. The CONSORT flow diagram with the number of schools and children is shown in Fig. 2.

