### Primary outcome

Fidelity to the four components of the HSS will be assessed through 13 indicators (Table 4) based on the dimensions adherence, dose, participant responsiveness, and quality of delivery [56, 57]. This information will be gathered through attendance logs, questionnaires answered by school staff and parents, and audio recordings of MI sessions. The primary outcome will be operationalized as an adherence score and a responsiveness score to the four intervention components. Adherence to three of the four components will be reported by parents and the nurse as yes/no. The classroom component will be reported by the teachers, and thus the score for this component will be the same for all children in the same class. The total adherence score will be from 0 to 4. Participant responsiveness measures how parents respond to and are engaged in the intervention and is measured on a scale from 1 to 5 (no appreciation to full appreciation) for each component with a total score of 4 to 20. Dose refers to exposure or the amount of the classroom component that has been delivered and received. This information will be obtained from the teachers who will use a logbook to report the proportion of teaching sessions performed, the proportion of lesson completion including length, and whether any adaptations and are made. Quality refers to the MI component. All MI sessions will be recorded and a random 10% of each nurses’ interviews will be coded for MI competence using the MITI protocol 4.2 [58] by reliable coders. Those indicators not included in the two primary outcomes will be tested separately between the Basic and Enhanced group of schools.

**Table 4 Tab4:** Indicators of fidelity to the HSS components

Component	Adherence (%) (yes/no)	Dose (%)	Participant responsiveness (scale 1–5)	Quality of delivery
Brochure with health information	Parents reading the brochure (P)^a^	NA	Parents’ appreciation of the brochure (P)^b^	NA
Motivational Interview (MI)	Parents receiving MI (N)^a^	NA	Parents’ appreciation of health counselling (P)^b^	Quality of MI score coded according to MITI 4.2 (C)
Classroom component	Teachers providing the classroom component (T)^a^	Proportion of classroom lessons performed (T) Proportion of lesson completion (T)	Teachers’ perceived child involvement and engagement (T) Parent’s appreciation of the homework (P)^b^	NA

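### The blinding scheme gives no masking to the coders who rate recorded MI sessions, although their score is compared between arms

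*Protocol article*

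**What the plan says.** The Randomisation and blinding section covers four parties. On the first two it states: "It is not possible to blind school staff and the research team to allocation". The other two, parents and children, are not to be told the allocation. It makes no exception for people who assess outcomes, and coders are not mentioned.

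The Primary outcome section lists the sources of fidelity data as attendance logs, "questionnaires answered by school staff and parents, and audio recordings of MI sessions". All MI sessions are to be recorded, and "a random 10% of each nurses’ interviews will be coded for MI competence using the MITI protocol 4.2 [58] by reliable coders". Table 4 places the resulting score in the quality-of-delivery column and gives the coder a separate informant letter, beside teacher, parent and school nurse. The score carries neither footnote that would put it into the adherence or the responsiveness score. For such indicators the plan is explicit: "Those indicators not included in the two primary outcomes will be tested separately between the Basic and Enhanced group of schools".

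**The concern.** Scoring MI competence is a judgement. The research team delivers the four additional strategies of the Enhanced arm (Table 3), and the stated hypothesis favours that arm. If a coder belongs to that team or is told the allocation, any drift in rating has a likely direction, and it would pass straight into a planned between-arm test. A recording is also the kind of material that can be rated without knowing the school or the arm. A sentence that rules out blinding for the whole research team therefore gives up a protection that is available for this indicator. At stake is the credibility of the only measure of how well, rather than whether, a component was delivered.

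**Working it through.** The protocol gives no figure to reproduce on this point. The check sets its statements side by side.

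1. **Where the indicator sits.** Table 4 lists 5 adherence, 2 dose, 5 responsiveness and 1 quality indicators: 5 + 2 + 5 + 1 = 13, which agrees with the text. Four adherence and four responsiveness indicators form the primary scores, which leaves 13 − 8 = 5 to be tested separately. MI quality is one of these five.

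2. **Who supplies each of those five, and what the blinding section says of them.**

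| Indicator | Informant | Blinding section |
|---|---|---|
| High-risk parents attending health care | Parent | Not told the allocation |
| Lessons performed | Teacher | Cannot be blinded |
| Lesson completion | Teacher | Cannot be blinded |
| Child involvement and engagement | Teacher | Cannot be blinded |
| MI quality | Coder | Not mentioned |

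The other eight indicators come from parents, nurses or teachers. The coder is thus the only informant type for which the scheme says nothing, unless coders count as research team, in which case it declares masking impossible.

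3. **Is it impossible for a coder?** For team members who deliver outreach visits, coaching, audit and feedback (Table 3), yes. For rating a recording, the document gives no reason:
   - No strategy in Table 3 is specific to the content of MI sessions.
   - MI training and supervision of nurses is described without distinction by arm (Step 3: Strategies performed by the research team).
   - Nurses' exchange of MI experience is in bundle 1, which all schools receive (Table 2).
   - Parents are not told the allocation, so the conversation should seldom reveal it.

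4. **Volume of material.** The number of coded recordings is not fixed by the document. Sampling is 10% per nurse, and the number of nurses is not given. As an assumption-based range per school and year, with 30 schools:
   - 800 consenting parents, all in one year: 800 / 30 × 0.10 = 2.7
   - 800 spread over two cohorts: 800 / 30 / 2 × 0.10 = 1.3
   - all of about 1400 families a year: 1400 / 30 × 0.10 = 4.7

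   This bears on the work of relabelling. It says nothing about the size of a bias.

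**The case against.** The strongest reply is that no text places the coders in the research team, says that they are told the allocation, or says that they are unmasked. Table 4 treats them as a separate informant. A reader might infer from the blinding section that the plan prescribes unmasked coding; the document does not support that, because it is silent on the coders' affiliation and on what they know. This part of the reply stands, and there is no contradiction between the two sections.

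A second reply is that an article may leave the handling of recordings to a fuller protocol, which could already provide for masking. This stands in part: such a provision may exist. But the article itself states a blinding scheme and claims impossibility for a whole group, so narrowing that claim and naming the coders corrects what is written and does not merely ask for detail.

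A third reply is that consequences are limited, since coding follows a named instrument on randomly chosen sessions. That is right, and it bounds the point without removing it. Random selection of sessions protects against selective choice of recordings, and a coding instrument structures the judgement; neither keeps the arm from the coder.

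**Conclusion.** The point holds as a cheap improvement. The stated scheme offers no masking for a subjective rating that "will be tested separately between the Basic and Enhanced group of schools", and the reason given for not blinding the research team does not extend to people who only rate recordings.

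The effect is confined to MI quality. It enters neither primary score, and the power calculation does not rest on it. The size of any bias cannot be computed from the document. A shift toward Enhanced is the plausible direction if coders know the arm and share the trial's hypothesis, but it is not demonstrated.

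Two stronger readings should be resisted. One is that the comparison of MI quality could not be defended at all; that would require knowing that coders were unmasked, which the document does not say. The other is that masking costs nothing; it takes some work, and it can occasionally fail. The conclusion rests on the assumption that a recording stripped of labels will usually not reveal the arm, which the content of Tables 2 and 3 makes reasonable but does not prove.

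**What to change.** In Randomisation and blinding, limit the impossibility statement to school staff and to team members who deliver bundle 2 or otherwise must know the arm. Add that MITI coding is done by people who do not deliver bundle 2 and are not told the allocation. Give each selected recording a random code, remove school, nurse and arm labels, and mix both arms in every coding batch. The key should stay with someone who does not code, and scores should be linked back to schools only after they are entered. If masking is not feasible, say why.

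The cost is a few sentences and the relabelling of the sampled files. A recording may still now and then reveal the school; coders can note when this happens so that it can be reported.

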**Fig. 2 Fig2:**
[figure not shown]
The CONSORT flow diagram of the IMPROVE study

### The Healthy School Start program

The HSS intervention is a universal intervention designed for all children in pre-school class over the course of one school year. It includes four intervention components described in the previous HSS study protocol [29] and briefly below.

#### Component 1: Health information

At the beginning of the school year parents will receive a brochure with health information based on the Swedish guideline for diet and physical activity [47]. The focus of the brochure is on evidence-based advice concerning parenting practices in relation to healthy food and family mealtimes, sweets, snacks, ice-cream, soft drinks, marketing of unhealthy products, fruit and vegetables, physical activity, sedentary behaviour, screen time, sleep, and cooperation between parents. The brochure is available in Swedish, English, Arabic and Somali and can also be downloaded from the project website.

#### Component 2: Motivational interviewing

MI is a client-centred, directive method for enhancing intrinsic motivation to behaviour change [48]. MI is today regarded as an evidence-based counselling method for behaviour change regarding diet and physical activity in adults [49] and shows promising results in parental support interventions on child health-related behaviours as well [50]. The MI session with the parents will be scheduled by the school nurse as part of the ordinary health visit of children in pre-school class. Parents will be offered a face-to-face MI by the school nurse conducted without the presence of the child and lasting for approximately 20 to 30 min. If special needs are encountered, a follow-up visit will be offered.

#### Component 3: Classroom activities with home assignments

Nine classroom sessions of approximately 30 min duration will be delivered by the teacher in preschool class based on a teacher’s manual developed for this program. In addition, a pedagogic workbook for children with home assignments to be performed together with parents will be handed out to each child. Teachers will receive video-recorded instructions on how to use the teacher’s manual and parents receive instructions and tips on how to practice positive parenting while doing the homework together with their child.

#### Component 4: Type 2 diabetes risk test online

This test contains eight questions and can be performed on paper in the health information brochure and/or online. FINDRISC is a validated tool used to identify individuals at high risk of developing T2D in the coming 10 years [51]. Questions included concern age, BMI, waist circumference, level of physical activity, consumption of vegetables, fruits and berries, history of antihypertensive medication, history of high glucose values and family history of diabetes. In case of medium or higher risk (≥12 points), the parent will be recommended to contact their primary health care centre to confirm prediabetes or T2D according to standard procedures. If the person has T2D or prediabetes then he/she will receive a general check-up, health behaviour counselling and appropriate treatment with yearly follow-up. All primary health care centres in the two municipalities will receive a yearly information letter explaining the intervention and the study.

### Standard practice in Swedish school health care

The national guidelines for school health care are formulated in general terms [30]. They require that the staff engages in health promotion and disease prevention activities and provide support to children in reaching educational goals. No referral is made to specific evidence-based procedures or practices. All school children are offered at least three visits to the school health care between pre-school class (age 6) to grade 9 (age 15). During the first visit to the school nurse in pre-school class the child is accompanied by parents or guardians for a discussion regarding the school situation, the child’s overall well-being, relations with friends, possible health and learning problems, dietary habits and physical activity. The child’s height and weight is measured and compared to standardised growth curves. Eyesight and hearing are also tested. If a child is overweight, additional counselling should be offered including a follow-up. In case of obesity, the school doctor should become involved, and if necessary, the child has to be referred to medical specialists in child obesity for treatment in dialogue with school health care and parents.

### Development of IMPROVE

Development of the IMPROVE study was done in four steps from September 2020 to June 2021 in collaboration with stakeholders in the municipalities and guided by the implementation strategies in the SISTER taxonomy [26].

#### Step 1: Exploring barriers and facilitators of implementation

Exploration of context-specific implementation barriers and facilitators was based on previous process evaluations of the HSS program [16, 38, 39, 41] and on two preparatory stakeholder workshops in each of the two municipalities participating in IMPROVE (Implementation strategy 1: Assess for readiness and identify barriers and facilitators). The CFIR framework was used as a guiding determinant framework due to its multilevel structure and its applicability to the municipality setting [20]. The workshops were held digitally in each municipality due to the Covid-19 pandemic prohibiting in-person workshops. Workshop 1 for municipality 1 was held in November, 2020, with 17 participants (4 from the research team, 2 from primary health care, 2 school principals, 5 school nurses, 3 teachers, and 1 central manager) and lasted for 2.5 h. Workshop 1 for municipality 2 was held in January, 2021, with 18 participants (4 from the research team, 3 from primary health care, 4 school nurses, 1 teacher, 2 school principals, 2 meal staff, and 2 managers) and also lasted for 2.5 h. Each workshop started with the research team presenting the HSS program and the purpose of the IMPROVE study and participants could ask questions for clarification. Then, a brainstorming session was conducted using a virtual white board where participants individually or in small groups for 30 min could contribute “notes” on perceived implementation determinants of HSS in their municipality within five categories: the school, primary health care, the home, the municipality, and “other areas”. In total 42 notes were submitted in municipality 1 of which 15 were marked as a barrier, 5 as both a barrier and a facilitator and 22 as facilitators. In municipality 2, 35 notes were submitted of which 13 were marked as barriers and 22 as facilitators.

After the first round of workshops, the research team coded the barriers and facilitators and grouped them according to the domains of CFIR. Two domains were added to the original CFIR framework: “Characteristics of intervention recipients” as already suggested by Barwick et al. [21] and “Inner setting primary care”. The determinants of intervention recipients (parents) were identified based on the experience of school personnel and confirmed by information from previous qualitative studies with parents participating in the program [16, 39, 40, 52]. The barriers and facilitators were then condensed by the research team into a list of more value-neutral implementation determinants in a consensus-based process. The determinants identified in the workshops were checked against previous process evaluations of the HSS intervention. In total 28 determinants were identified (Table 1) and exemplified by notes made during the workshops by the participants.

**Table 1 Tab1:** Implementation determinants identified by stakeholders

CFIR domain	Determinants of implementation	Example of notes made by workshop participants
Intervention characteristics (HSS)	1. Program supported by guidelines and curriculum	*“The content/purpose can be linked to the curriculum”*
	2. Involvement of parents	*“Children and parents can get support for a healthier lifestyle and parents can get help with strategies to reach them. Good with MI for self-motivation”*
	3. Consensus on healthy lifestyle	*“Very good with increased and equal knowledge to students and parents about diet, exercise, and health, regardless of background and resources*”
	4. Clarity of material and instructions for use	*“Get a teaching plan for an important part of the student’s development towards a healthy life”*
Outer setting (municipality)	5. Societal action and cooperation	*“That these social institutions work together on the health of the population. Can increase understanding of each other’s mission but also that we share the health mission to reduce social health inequalities”*
	6. Environmental factors	*“In disadvantaged settings, it can be an economic issue, fruits and vegetables are relatively expensive, junk food cheaper, parents can’t afford to let children practice sports”*
	7. Local policies	*“Link to activities and policies that are decided upon”*
Inner setting #1 (school)	8. Common goals and collaboration in school	*“That the school works towards common goals, school health care and teachers work with health promotion and start from the same point of departure and “language” when talking to children and parents”*
	9. Communication and collaboration between school-home	*“Good to have increased consensus between school staff and parents regarding good nutrition and practices around this”*
	10. Continuity in staffing and work routines	*“That there may be staff changes that make implementation difficult both within school health care and teachers”*
	11. Leadership in school	*“Important that all principals endorse the project at their school”*
	12. Visible priority of health	*“That the school works towards a common goal and is consistent in its communication with parents”*
Inner setting #2 (primary care)	13. Communication within and between primary health care units	*“It will be a challenge to communicate to all primary health care centres and to all its individual employees about what the project is about and what help should be offered to those who contact them”*
	14. Time for administration in primary health care	*“Fear that there will be a lot of administrative work for the caregivers. Important to avoid”*
	15. Collaboration between primary care and school	*“Proposal to address IMPROVE at an annual meeting between primary care and school health care”*
	16. New target groups	*“At the primary health care centre you can find other health risks in the parents if they have high blood sugar”*
	17. Early prevention	*“A good opportunity for primary care to work more with prevention and to reach risk groups in time”*
Intervention recipients (parents)	18. Family consensus on healthy lifestyle	*“Very good with increased and equivalent knowledge to students and parents about diet, exercise and health regardless of background and preconditions”*
	19. Parents’ knowledge and skills	*“Parents are included in their children’s homework and together they learn about good habits. Teachers follow up and remind about the homework”*
	20. Socioeconomic and cultural factors, language	*“Socio-economically weak areas - risk of lower adherence to homework being completed - high risk of attrition”*
	21. Parents’ perceived need and readiness	*“Children with overweight/obesity often have parents with the same problems. Difficult to motivate for lifestyle changes”*
	22. Parents’ engagement in children’s schoolwork	*“Poor adherence to homework. The resourceful do tasks with the children but not those who need them”*
Individual providers (school and primary care staff)	23. Providers’ attitudes towards the program	*“Motivated preschool teachers who are happy to be involved in development”*
	24. Providers’ competence and self-efficacy	*“Great increase in skills for staff, raising equality”*
	25. Providers’ experience of workload and responsibility	*“Can be experienced by school staff as an increased workload. A change in working routines is always demanding”*
Process	26. Time for planning and executing program in school	*“It is important that time is given for planning and that it is clear how much time is required for all steps”*
	27. Communication and collaboration within school regarding process	*“That all material from Karolinska Institutet is sent out before the work at the schools takes place, which creates time for good planning in the classes”*
	28. Sustainability of program	*“That the project continues, that it is not dependent on individuals but can continue regardless of what the organisation looks like in schools and in the central administration”*

#### Step 2: Tailoring of implementation strategies

The determinants identified by stakeholders were discussed among the research team and preliminary strategies were mapped to these determinants through an internal consensus process (Strategy 17: Tailor strategies). The selection was also influenced by the work of Lyon et al. [53] who had described the most important and feasible strategies in the school context. In the second workshop in January (municipality 1) and February (municipality 2) with the same stakeholders, the implementation determinants identified in workshop 1 and the pre-selected strategies were presented. Stakeholders could then provide feedback based on their expertise and experience regarding the form and function of each strategy. No more strategies were added at this stage. After the stakeholder workshops, the scientific advisory panel was consulted to develop a final consensus on the most appropriate implementation strategies to use, which resulted in minor adjustments. The final selection of implementation strategies targeting the context-specific implementation determinants identified in Step 1 is shown in Table 2 (Basic). Based on our previous experience with the HSS program, these are regarded as a minimum to implement the HSS with reasonable fidelity in addition to first receiving formal commitment from the school principal.

**Table 2 Tab2:** Implementation strategies to be deployed by all schools (bundle 1)

Implementation strategies (SISTER strategy number)	Determinants targeted	Description of the strategy	Actors	Target
Conduct local consensus discussions (23)	1. Program supported by guidelines and curriculum 5. Societal action and cooperation 8. Common goals and collaboration in school 10. Continuity in staffing and work routines 11. Leadership in school 12. Visible priority of health 23. Providers’ attitudes towards the program 27. Communication and collaboration within school 28. Sustainability of program	Introduction of the HSS to all school personnel with the help of material to create commitment and reach consensus	School principal	School personnel
Distribute educational materials (42)	8. Common goals and collaboration in school 24. Providers’ competence and self-efficacy	Order educational material at the beginnning of the new school year (manual, teachers manual, workbook for children, posters etc.) and distribute it	School health team	School personnel
		Listen to educational lectures posted on the HSS website at least once every school year whenever it fits with the schedule	School health team	School personnel
Organize school personnel implementation team meetings (32)	25. Providers’ experience of workload and responsibility 26. Time for planning and executing the program in school 27. Communication and collaboration within school regarding process	Form a health team including a teacher representative and appoint a coordinator to follow up and reflect on how to devide the practical work with the HSS, the implementation process, knowledge exchange, and how to support one another’s learning	School principal and health team	School health team
Peer-assisted learning (13)	3. Consensus on healthy lifestyle 4. Clarity of materials and instructions for use 8. Common goals and collaboration in school 23. Providers’ attitudes towards the program24. Providers’ competence and self-efficacy 26. Time for planning and executing in school 27. Communication and collaboration within school regarding process	Watch the introductory video to the classroom component, discuss a plan for implementation, how to engage parents in the home assignments	Teachers	Teachers
		Exchange of knowledge and experience in MI	School nurses	School nurses
		Internal and external meetings for inspiration, knowledge exchange and how to organise the work	School health team	School personnel
Change/alter environment (54)	6. Environmental factors 7. Local policies	Discussion regarding the possibility to make changes to support healthy lifestyle within and around the school	School health team	Community, school and after-school care
Prepare families and students to be active participants (55)	2. Involvement of parents 9. Communication and collaboration school-home 18. Family consensus on healthy lifestyle 19. Parents’ knowledge and skills 20. Socioeconomic and cultural factors, language 21. Parents’ perceived need and readiness 22. Parents’ engagement in the HSS	Announcement that the school is a health promoting school	School principal	Parents
		Introduction of the HSS at the first meeting with new parents through a film, giving the rational for the intervention, in basic Swedish and texted in other common languages	School personnel	Parents
		Information sent out in the newsletter to families of the start of the HSS. Encouragement to consult the HSS website for further information and material	School personnel	Parents

*HSS* Healthy School Start; *MI* Motivational interviewing

Six strategies will be deployed by school personnel (Table 2), supported by the material provided by the research team. At the start of the intervention and repeated yearly, the principal initiates meetings with all staff to present the HSS program and reach consensus on its execution (Strategy 23: Conduct local consensus discussions). Next, educational materials are ordered by the schools, and relevant public health lectures are made available on the project website (Strategy 42: Distribute educational materials). A health team (standard in Swedish schools) including teachers is formed and a coordinator is appointed, who will also be the contact person for the research team (Strategy 32: Organize school personnel implementation team meetings). Both teachers and school nurses engage in peer-assisted learning and make a timeplan for their respective intervention components (Strategy 13: Peer-assisted learning). If necessary, the school environment is changed to become more health promoting (Strategy 68: Change/alter environment), which may include the physical and social environment. Finally, various efforts are made to prepare families to be active participants (Strategy 58: Prepare families and students to be active participants) and consent to take part in the study through means such as information meetings, written material and a film promoting the HSS and the IMPROVE study.

Table 3 shows four additional strategies delivered to the Enhanced group only. These strategies can be characterised by regular fidelity monitoring, coaching and on-demand assistance provided by the research team to school personnel.

**Table 3 Tab3:** Implementation strategies offered to group 2 schools only (bundle 2)

Implementation strategies (SISTER strategy number)	Determinants targeted	Description of the strategy	Actor	Target
Conduct educational outreach visits (38)	23. Providers’ attitudes towards the program 24. Providers’ competence and self-efficacy	Yearly presentations to schools on topics in public health of their choice and relevant to the intervention	Research team	School personnel
Promote network weaving (33)	13. Communication within and between primary health care centres 14. Time for administration in primary health care 15. Collaboration between primary care and school 16. New target groups 17. Early prevention 28. Sustainability of program	Send out yearly information letter to primary health care centres about the HSS program and the IMPROVE study. Encourage yearly meetings to establish social networks, promote information sharing, collaborative problem-solving and shared goals regarding family health	Research team	School health care and primary care
Provide ongoing consultation/coaching (44)	23. Providers’ attitudes towards the program 24. Providers’ competence and self-efficacy	Yearly audit and feedback through a written report on the fidelity score and performance of implementation strategies with coaching how to improve. E-mail sent four times per year to the school health team coordinator to offer assistance and help with problem solving	Research team	School personnel
Obtain and use student and family feedback (8)	23. Providers’ attitudes towards the program	Yearly feedback on parents’ attitude and perception of the program	Research team	School personnel

